### Sample size

The sample size is calculated for the noninferiority study comparing change in visual acuity for patients treated by nurses to those treated by physicians.

#### Sample size considerations

In contrast to earlier studies comparing the effect of two different anti-VEGF drugs or the effect of different anti-VEGF treatment strategies, we want to test the effect of two different professions performing the treatment. Historical data from large randomized clinical AMD trials found the mean change in visual acuity during the first year of treatment to be 6–7 letters (1,2–1,4 lines) [18]. The CATT study was as the present study designed as a noninferiority study. As the noninferiority margin (δ_L_) should be less than the observed change in visual acuity, five letters (one line on the visual acuity chart) was chosen as the acceptable difference for the tested treatment to be considered noninferior to the reference treatment. However, in a study of the safety of nurse-administered IVI, a noninferiority margin of five letters may be considered too wide.

First the study population in the present study is not as homogenous as the before mentioned study since it includes both patients with AMD, RVO and DME. There is an anticipated difference in treatment response in these three conditions. Second, the majority of study participants will already have received several IVI before inclusion in the study and in these patients we do not expect major changes in visual acuity during the study period. Third, we should consider the ethical aspect of having a wide noninferiority margin; if it is right to sacrifice visual acuity to gain the possible benefit of cost savings by nurses treating the patients. Taking these aspects into consideration, we find that the noninferiority margin should not exceed three letters. In other words, the present study will test whether IVI administered by nurses is not less effective than treatment by physicians, by more than three letters.

We assume that the standard deviation (SD) of the distribution of changes, σ, will be 10 letters. This is again less than in the studies forming the basis for IVI of anti-VEGF, finding a SD of 15 letters reasonable the first year. The second year, however, the standard deviation, dropped to 11 letters and in our study we do assume 10 letters would be reasonable [8].

The anticipated true difference between the treatment groups is 0. That is, the effect of the treatment is expected to be equal in the two groups.

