### Trial recruitment

All patients with AMD, RVO or DME that are eligible for anti-VEGF IVI and able to give an informed consent are invited to participate. Both newly referred patients during 01.03.15–01.01.16 as well as patients that are already receiving anti-VEGF IVI fulfil the inclusion criteria.

Patients with ocular pathology eligible for anti-VEGF IVI other than the abovementioned conditions and inability to provide an informed consent do not fulfil the inclusion criteria and are excluded.

Information about the study will be given either face-to-face in the department or via a phone call and will also be handed out in writing. The patients will receive trial information at least 24 h before being asked to give an informed consent. If the patient agrees to enter the trial, written informed consent will be obtained. Consent forms will be stored in a locked safe to which only study management has access. Patients who do not consent to the trial will be treated according to standard care.

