#### Sample size and power calculation

The sample size is calculated by using the abovementioned assumptions and the sample size formula for comparing two means in a noninferiority trial (SPSS Sample Power 3).

Choosing a noninferiority margin δ_L_ =3, standard deviation SD = 10 and a significance level of 0.05, 140 participants is required in each group to have a power of 80 % to reject the null hypothesis, H_0_ ≤ - δ_L_ and conclude that nurses are treating the patients equally safe as or better than physicians, if the null hypothesis is true.

We anticipate the percentage of patients completing the final visit at 12 months to be 92 % as a dropout of 8 %, including patient death and illness, is not uncommon in similar trials. This means that to make sure that 140 participants complete a 12-month observation period; at least 152 patients should be included in each of the study arms.

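### The planning SD of 10 letters is below both SDs the protocol cites, with no reason given for going under 11; at SD 11 the power is about 74%, not 80%

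*Protocol article*

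**What the plan says.** Under Sample size considerations the protocol fixes the planning value: "We assume that the standard deviation (SD) of the distribution of changes, σ, will be 10 letters". It acknowledges that this is smaller than in the trials on which the treatment rests, and describes those trials as "finding a SD of 15 letters reasonable the first year". It then continues: "The second year, however, the standard deviation, dropped to 11 letters and in our study we do assume 10 letters would be reasonable". The margin is set in the same section ("we find that the noninferiority margin should not exceed three letters"), and so is the expected effect: "The anticipated true difference between the treatment groups is 0".

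Sample size and power calculation uses "standard deviation SD = 10 and a significance level of 0.05" to reach 140 completers per arm for 80% power, and at least 152 enrolled per arm after 8% dropout.

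Three other statements bear on the SD:

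- Trial recruitment admits newly referred patients "as well as patients that are already receiving anti-VEGF IVI fulfil the inclusion criteria".
- Sample size considerations expects most participants to be previously treated, with little change in acuity. It also says: "First the study population in the present study is not as homogenous as the before mentioned study", because AMD, RVO and DME are combined.
- Statistical methods names a t-test on change scores for the primary objective. It adds a regression adjusted for diagnosis; adjustment for first or follow-up treatment depends on sufficient numbers.

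**The concern.** The section cites two SDs and plans on a value below both. A mostly pre-treated sample is a fair reason to prefer 11 to 15. Nothing in the text explains the further step from 11 to 10: no pilot data, no figures from the clinic's own patients, and no allowance for covariate adjustment. Two stated features of the trial, first-treatment patients and a mixture of diagnoses with different expected responses, would tend to widen the spread of change scores in an unadjusted comparison.

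What is at stake is how an inconclusive result would be read. If nurses and physicians are truly equivalent, the reader is told that noninferiority will be missed about 20% of the time. At the nearest cited SD it would be missed about 26% of the time.

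**Working it through.** **Inputs.** Margin δ = 3, SD σ = 10, true difference 0, n = 140 completers per arm, 8% dropout, 1:1 allocation, all from the protocol. Cited alternatives for σ are 11 and 15. The level of 0.05 is not labelled one- or two-sided. It is taken as one-sided because that reproduces the stated number; one-sided 0.025 would need 175 per arm.

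**Reproducing the stated figure.**

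n = 2σ²(z₀.₉₅ + z₀.₈₀)²/δ² = 2 × 100 × (1.645 + 0.842)²/9 = 137.4, so 138 per arm (139 with the exact noncentral t). The protocol's 140 agrees. Dropout: 140/0.92 = 152.2, against 152 stated.

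**Power at other SDs.** Power = Φ(δ/(σ√(2/n)) − 1.645). With n = 140, √(2/140) = 0.1195.

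| SD | SE of difference | δ/SE | Power (normal) | Power (noncentral t) | Completers per arm for 80% |
|---|---|---|---|---|---|
| 10 | 1.195 | 2.510 | 80.7% | 80.5% | 138–139 |
| 11 | 1.315 | 2.282 | 73.8% | 73.6% | 167 |
| 15 | 1.793 | 1.673 | 51.1% | 51.0% | 310 |

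**If nobody drops out.** With n = 152 per arm and σ = 11, SE = 11 × √(2/152) = 1.262, δ/SE = 2.378 and power is 76.8%.

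**Slack in the assumption.** The largest SD that keeps 80% at 140 per arm is 3/(0.1195 × 2.486) ≈ 10.09.

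**Direction of the first-treatment effect.** If a share f of patients has SD 15 and the rest SD 11, the within-group variance is 225f + 121(1 − f). This exceeds 121 for any f above 0, and any difference in mean change between the two groups adds to it. The protocol does not state f, so only the direction follows.

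**What adjustment would have to achieve.** To bring a raw SD of 11 down to a residual SD of 10, covariates must explain 1 − 100/121 = 17% of the variance. To reach the 10.09 limit they must explain 1 − 10.09²/121 = 16%.

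**The case against.** The strongest reply is that this is a disclosed assumption and not a miscalculation. That stands: the number per arm is right for the SD used, and the text says openly that the SD is smaller than in earlier trials. A reader might infer that the sample size was computed wrongly, and the documents do not support that.

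A second reply is that the SD fell from 15 to 11 by the second year, so a group mostly treated for some time could plausibly be a letter lower. It could, but the protocol does not make the argument or offer data for it.

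Third, the remark on heterogeneity is made to justify a narrower margin and concerns differences in mean response by diagnosis, which the diagnosis-adjusted regression can remove. This is correct as far as it goes. The sample size nevertheless rests on the raw SD and the named primary test is an unadjusted t-test, so that gain is not yet in the plan.

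Fourth, the consequence is limited. A larger SD does not raise the chance of falsely declaring noninferiority. With 140 per arm, the half-width of the two-sided 90% interval grows only from 1.645 × 1.195 = 1.97 to 1.645 × 1.315 = 2.16 letters, and the final interval will show the precision achieved. This is why the remedy is small, but it does not make the 80% correct at SD 11.

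Finally, 304 is a minimum and actual enrolment is not given, so 140 completers per arm is the planned number and not necessarily the final one.

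**Conclusion.** The 80% power holds at SD 10 and at neither SD the protocol cites. Because most participants are expected to be pre-treated, 11 is the relevant comparator. Power there is about 74%, a shortfall of about 6 points, or about 77% with complete follow-up of 152 per arm. This rests on a 3-letter margin, a one-sided 5% level, no true difference and an unadjusted comparison.

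Two stronger readings are tempting. One is that power is really about 51%. That figure applies to SD 15, which describes a wholly first-year population that this trial does not expect. The other is to put a single lower figure on the mixed population. That needs the share of first-treatment patients, which is not stated. It would also mean applying the 6–7 letter first-year gain, which the protocol cites from AMD trials, to RVO and DME. The documents support saying that first-treatment patients lower the power below the SD 11 figure, but not by how much.

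This is an optimistic planning assumption without a stated justification. It weakens the power claim, not the validity of the test.

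**What to change.** 1. State power as about 80% at SD 10 and about 74% at SD 11 for 140 completers per arm. Add that first-treatment patients would lower it further, by an amount that depends on their share. If the sponsor has data supporting an SD below 11, cite them.
2. Before unblinding, compute and report the pooled SD of the 12-month change without reference to arm. According to Trial status, data collection continues until January 2017, so this can still be done.
3. Before unblinding, make the primary noninferiority comparison a linear model for change in acuity, adjusted for baseline visual acuity, diagnosis and first or prior treatment, in place of the unadjusted t-test. Judge its confidence limit against the same 3-letter margin. Whether the covariates reach the 17% needed at SD 11 is not known in advance, so no gain should be promised.

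The cost is a less favourable power statement, one blinded calculation and an amendment to the primary analysis. Recruitment has closed and no added enrolment is proposed.

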#### Sample size and power calculation

The sample size is calculated by using the abovementioned assumptions and the sample size formula for comparing two means in a noninferiority trial (SPSS Sample Power 3).

Choosing a noninferiority margin δ_L_ =3, standard deviation SD = 10 and a significance level of 0.05, 140 participants is required in each group to have a power of 80 % to reject the null hypothesis, H_0_ ≤ - δ_L_ and conclude that nurses are treating the patients equally safe as or better than physicians, if the null hypothesis is true.

We anticipate the percentage of patients completing the final visit at 12 months to be 92 % as a dropout of 8 %, including patient death and illness, is not uncommon in similar trials. This means that to make sure that 140 participants complete a 12-month observation period; at least 152 patients should be included in each of the study arms.

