### Objectives

The primary objective is to evaluate the safety of nurse-administered IVI of anti-VEGF compared with physician-administered IVI.

The secondary objectives are:to evaluate cost of nurse-administered IVI of anti-VEGF compared with standard careto evaluate patient satisfaction of nurse-administered IVI of anti-VEGF compared with standard care

For the primary objective the evaluation will be performed using a noninferiority test, to test whether the nurses are treating the patients equally safe or better than the reference group, i.e physicians. More specifically, the null (H_0_) and alternative (H_A_) hypotheses are:$$ {\mathrm{H}}_0:\ {\upmu}_{\mathrm{NURSES}}\hbox{--}\ {\upmu}_{\mathrm{PHYSICIANS}}\le -{\updelta}_{\mathrm{L}}\kern0.37em \mathrm{and}\;{\mathrm{H}}_{\mathrm{A}}:\ {\upmu}_{\mathrm{NURSES}}\hbox{--}\ {\upmu}_{\mathrm{PHYSICIANS}}> - {\updelta}_{\mathrm{L}}, $$

where μ _i_ is the mean change in visual acuity from first visit (baseline) to last visit 12 months later in group i, and δ_L_ is “the noninferiority margin”, which is the maximum clinically acceptable difference in change, for treatment by nurses to be considered noninferior to the reference treatment, δ_L_ >0

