The present study is not dimensioned to evaluate whether there is an increased risk of complications that need treatment, since the rates of these complications are very low. Given that nurse-administered IVI is safe, we find the secondary outcomes equally relevant and of great importance to examine adverse events, patient satisfaction and economic aspects.

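### Rejecting H0 shows only that nurses' mean acuity change is not worse by more than three letters; the protocol words this as safety equal to or better than physicians'

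*Protocol article*

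**What the plan says.** The Protocol article attaches two different conclusions to the same noninferiority test.

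- **Broad wording.** Objectives says the test is used "to test whether the nurses are treating the patients equally safe or better than the reference group". Sample size and power calculation says that rejecting H0 allows the trial to "conclude that nurses are treating the patients equally safe as or better than physicians".
- **Narrow wording.** The formal hypotheses in Objectives set H0 as a nurse-minus-physician difference in mean change at or below minus the margin, and the alternative as a difference above it. In Sample size considerations the authors write "we find that the noninferiority margin should not exceed three letters", and then that the study will test whether "IVI administered by nurses is not less effective than treatment by physicians, by more than three letters".

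The Discussion has a similar tension about safety. It expresses confidence that the design is strong enough to judge whether nurses inject as safely as usual care. It later says: "The present study is not dimensioned to evaluate whether there is an increased risk of complications that need treatment".

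**The concern.** The alternative hypothesis covers every true difference above minus three letters. That includes deficits between 0 and 3 letters as well as equality and benefit. A significant result therefore rules out a mean deficit of three letters or more and does no more than that. *Equal* and *better* are further claims, which this test neither makes nor protects.

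The wording matters because the result may be used to support moving injections from physicians to nurses. Sample size considerations itself raises the ethics of trading acuity for cost savings and narrows the margin for that reason. A reader of the result should be told what deficit was ruled out, not that there was none. Likewise, a result on mean acuity should not be read as a finding about injection complications, which the Discussion says the study was not sized to address.

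**Working it through.** **Inputs, all from the Protocol article**

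- Margin: 3 letters (Sample size considerations).
- SD of change: "in our study we do assume 10 letters would be reasonable".
- Level and size: "a significance level of 0.05, 140 participants is required in each group"; power 80% (Sample size and power calculation).
- Anticipated true difference: 0 (Sample size considerations).
- Sidedness: not stated. The hypotheses are one-sided.

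**Step 1. Reproduce the stated size.**

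n per arm = 2 × SD² × (z for level + z for power)² / margin²

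- One-sided 0.05: 2 × 100 × (1.645 + 0.842)² / 9 gives 138 (139 with the noncentral t). This agrees with 140.
- One-sided 0.025: 2 × 100 × (1.960 + 0.842)² / 9 gives 175 (176 with t). This does not agree.

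The figures below therefore use one-sided 0.05. The sample-size arithmetic is not at fault.

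**Step 2. Find the worst observed result that passes.**

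- Standard error of the difference: 10 × √(2/140) = 1.195 letters.
- Noninferiority is declared when the observed difference exceeds −3 + 1.645 × 1.195 = −3 + 1.966 = −1.03 letters.
- Example: an observed difference of −1.0 has a two-sided 90% interval of −1.0 ± 1.97, that is −2.97 to 0.97. It passes, with nurses numerically worse and an interval reaching almost to the margin.

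**Step 3. Find how often the test passes at given true differences.**

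P(pass) = Φ((3 + true difference)/1.195 − 1.645)

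| True difference (letters) | P(pass) |
|---|---|
| 0 | 81% |
| −1 | 51% |
| −2 | 21% |
| −3 | 5% |

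At one-sided 0.025 with the same 140 per arm, the cut-off is −0.66 letters and P(pass) at a true 1-letter deficit is 39%. The sizes change but the logic does not.

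**Step 4. Find what *better* would need.**

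The lower confidence limit must lie above 0. At the same one-sided 5% level, that means an observed nurse advantage above 1.645 × 1.195 = 1.97 letters. The cut-offs for the two claims, −1.03 and +1.97, are three letters apart, which is exactly the margin. One rejection cannot serve for both.

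**Step 5. Set the safety statements side by side.**

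The Discussion's claim about strength of design is unrestricted, while its later statement excludes an increased risk of complications needing treatment. Both hold together only if the first is read as a claim about visual acuity, and the text does not say so.

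**The case against.** The strongest reply is that the protocol already defines its claim correctly. In Objectives the loose phrase is followed at once by formal hypotheses and a definition of the margin as the largest clinically acceptable difference. Sample size considerations gives the right sentence, and Statistical methods commits to CONSORT reporting for noninferiority trials. The Abstract also defines safety, for the primary outcome, as mean change in visual acuity. On this view the fault is an inconsistent gloss, and no hypothesis, test or sample size is wrong. That stands, and it limits the point to wording. It does not remove it: even with safety defined as mean acuity, equality or superiority does not follow from rejecting H0, and the faulty sentence is the one that states the trial's conclusion.

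A reader might infer several stronger things that the documents do not support.

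- **That the test lets a three-letter deficit through.** A true 3-letter deficit passes only 5% of the time, and an observed deficit above about 1.0 letter fails. Passing at true deficits of 1 or 2 letters is no design error, since both lie inside the prespecified margin.
- **That the trial could pass while demonstrating that nurses are worse.** At the planned precision it could not. The worst passing result, −1.03, has an upper 90% limit of −1.03 + 1.97 = 0.94, which is above 0.
- **That mean acuity is an unfit safety endpoint because it barely reacts to rare severe harm.** The protocol gives no complication rate beyond calling it very low, and no letters lost per event, so any figure is an assumption. If 2% of nurse-arm patients lost an extra 30 letters, the pass rate would be 61%; that is a visible drop from the 81% with no harm. The Discussion also gives reasons for choosing acuity, including faulty drug delivery and overlong treatment intervals. These could affect many eyes modestly, which a mean can detect.
- **That complications are ignored.** Ocular adverse events needing treatment are a named secondary outcome recorded on a dedicated form, and the lack of power for them is disclosed.

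**Conclusion.** The point holds as an error in the stated conclusion. Objectives and Sample size and power calculation claim more than the alternative hypothesis contains and more than Sample size considerations says. On the plan's own values (140 completers per arm, SD 10, one-sided 0.05 as inferred from the sample size), a pass is compatible with an observed nurse deficit of up to about 1.0 letter. It occurs 51% of the time at a true 1-letter deficit. That a pass does not establish equality or superiority needs no assumption, because it follows from the form of the hypotheses.

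The Discussion's general safety claim also goes beyond its own statement on complications and should be read as limited to visual acuity. The choice of endpoint, the margin and the sample size are not called into question here.

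**What to change.** 1. In Objectives and in Sample size and power calculation, replace the conclusion with the statement already in Sample size considerations: mean 12-month change in visual acuity with nurse injection "is not less effective than treatment by physicians, by more than three letters".
2. Reserve *better* for a lower confidence limit of the nurse-minus-physician difference above 0.
3. In the Discussion, limit the claim about judging safety to visual acuity, so that it agrees with the statement on complications.
4. As supportive reporting, not as a condition for the primary conclusion:
   - Give ocular adverse events per arm with exact 95% confidence intervals. These would show how little a low count excludes: no events in 140 patients leaves a one-sided 95% upper bound of 1 − 0.05^(1/140) = 2.1%.
   - Give the proportion per arm losing 15 letters or more, with a 95% confidence interval for the difference.

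The cost is a few sentences and one table from data already being collected. The downside is a narrower headline claim. No new patients, visits or measurements are needed.

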## Discussion

The primary objective of the study is to evaluate safety of nurse-administered IVI of anti-VEGF compared with physician-administered IVI. Anti-VEGF IVI represents a considerable workload on ophthalmologic clinics and will probably continue to do so in the near future. Extending the roles of other health workers may relieve this workload from ophthalmologists and several clinics have had good experience training nurses to perform IVIs independently [11–14]. However, none have as far as we know, investigated the safety, cost and patient acceptance of independent IVI administration by trained nurses in a RCT.

We have chosen visual acuity as the primary outcome of the present study. The major goal is to investigate safety of nurse-administered IVI and visual acuity is recommended by health authorities in clinical trials when investigating this outcome [19]. Furthermore, most patients probably want to be sure that nurse-administered IVI does not pose any increased risk of deteriorating their sight.

It is conceivable that several aspects of the IVI procedure may affect visual acuity: the injection technique may be unsatisfactory performed so that the drug may not be administered correctly into the tissue where it acts, contraindications may be misinterpreted putting the patient at risk of complications or the treatment plan may be misinterpreted so that patients receive IVI with too lengthy intervals. The training and certification of the nurses is a key in this context, and the present study is in many ways a test of whether the training of nurses was adequate or not.

We believe that the design of the study, the randomization procedure and outcome measurements will be of sufficient strength and quality to evaluate if nurses are performing IVIs as safe as the standard care. Both newly remitted patients and patients treated before are invited to participate in the study and our experience so far is that it is easier including patients familiar with the treatment than the newly remitted patients. If few newly diagnosed patients are included, the interpretation of results will be for the follow-up patients only.

The present study is not dimensioned to evaluate whether there is an increased risk of complications that need treatment, since the rates of these complications are very low. Given that nurse-administered IVI is safe, we find the secondary outcomes equally relevant and of great importance to examine adverse events, patient satisfaction and economic aspects.

